## Abstract

**Background:**

Reducing the disease burden of major depressive disorder (MDD) is of major public health relevance. The prevention of depression is regarded as one possible approach to reach this goal. People with multiple risk factors for MDD such as chronic back pain and subthreshold depressive symptoms may benefit most from preventive measures. The Internet as intervention setting allows for scaling up preventive interventions on a public mental health level.

**Methods:**

This study is a multicenter pragmatic randomized controlled trial (RCT) of parallel design aiming to investigate the (cost-) effectiveness of an Internet- and mobile-based intervention (IMI) for the prevention of depression in chronic back pain patients (PROD-BP) with subthreshold depressive symptoms. eSano BackCare-DP is a guided, chronic back pain-specific depression prevention intervention based on cognitive behavioral therapy (CBT) principles comprising six weekly plus three optional modules and two booster sessions after completion of the intervention. Trained psychologists provide guidance by sending feedback messages after each module. A total of 406 patients with chronic back pain and without a depressive disorder at baseline will be recruited following orthopedic rehabilitation care and allocated to either intervention or treatment-as-usual (TAU). Primary patient-relevant endpoint of the trial is the time to onset of MDD measured by the telephone-administered Structured Clinical Interview for DSM (SCID) at baseline and 1-year post-randomization. Key secondary outcomes are health-related quality of life, depression severity, pain intensity, pain-related disability, ability to work, intervention satisfaction and adherence as well as side effects of the intervention. Online assessments take place at baseline and 9 weeks as well as 6 and 12 months post-randomization. Cox regression survival analysis will be conducted to estimate hazard ratio at 12-month follow-up. Moreover, an economic analysis will be conducted from a societal and public health perspective.

**Discussion:**

This is the first study examining an IMI for depression prevention in a sample of chronic pain patients. If this implementation of a depression prevention IMI into orthopedic aftercare proves effective, the intervention could be integrated into routine care with minimal costs and extended for use with other chronic diseases. Results will have implications for researchers, health care providers and public health policy makers.

**Trial registration:**

The trial is registered at the WHO International Clinical Trials Registry Platform via the German Clinical Studies Trial Register (DRKS): DRKS00007960. Registered 12 August 2015.

## Background

Major depressive disorder (MDD) is related to high disease burden for both people affected and society [1]. In a recent literature review investigating global variation in the prevalence and incidence of MDD, a global point prevalence of 4.7%, a lifetime prevalence between 10 and 15% and a global incidence of 3.0% have been reported [2, 3]. It is estimated that existing psychological and pharmacological treatments have the potential to avert only 36% of the burden of MDD, and only when assuming perfectly efficient provision of existing treatments in terms of coverage, patient compliance, an d clinician competence [4, 5]. Thus, we are either in need of more powerful interventions for treating depression or we should aim at diminishing the likelihood of developing depression in the first place, highlighting prevention of depression as a promising approach. Recent research suggests that psychological preventive interventions such as cognitive behavioral therapy (CBT) or interpersonal psychotherapy have the potential to prevent a clinically significant number of new depression cases [6]. A meta-analysis of 32 randomized controlled trials (RCTs) reported a reduced incidence rate for MDD of 21% (incidence rate ratio = 0.79, 95% confidence interval: 0.69–0.91) when comparing psychotherapy-based preventive interventions with usual care or wait list conditions.

While the effectiveness of preventive interventions seems sufficiently documented, it remains challenging to identify target populations that benefit most from preventive measures [7]. According to Cuijpers and colleagues [8] two factors need be taken into account: the “impact” and the “effort” of preventive measures. An adequate “impact” means that prevention must lead to a substantial reduction of total disease burden. Therefore, a substantial proportion of new cases must be prevented if assembled risk indicators are fully blocked. A reasonable level of “effort” is primarily defined as a low number needed to be treated (NNT) to prevent one new case of MDD. Additionally, persons at risk should be easily identifiable and interventions should not only be cost-effective but also low priced to allow for their implementation at a population level.

From this viewpoint, chronically medically ill patients appear to be a meaningful target population for the prevention of MDD, given the substantially increased prevalence for MDD in this population compared to the general population [9, 10]. In addition, comorbid MDD in medically ill patients is associated with numerous negative implications such as problems in the physician-patient relationship, increased risky health-related behaviors, higher medical symptom burden, medical complications, lowered quality of life and increased mortality [11, 12]. Within the group of medically ill persons, back pain is one of the most common conditions [10, 13] and is associated with a two to three-fold increased risk for MDD [14]. In addition, depression is one of the core predictors of persistent pain symptoms, increased pain related disability, and poor treatment outcomes, and is associated with increased morbidity and health care costs as well as diminished quality of life [11, 12, 15–17].

The benefits of prevention can be multiplied by focusing on patients who already show some depressive symptoms due to several reasons. First, subthreshold depressive symptoms are an additional risk indicator for MDD [18, 19]. Multiple risk groups have increased specificity for prevention measures which leads to a reduction of NNT (“effort”) [20] and leading to greater cost-effectiveness of preventive interventions. Second, by lowering the NNT, the number of persons who are not in need of a preventive intervention, but receive it, will be reduced. Third, subthreshold depression itself is a considerable disease burden for people affected and for society [21, 22]. A successful preventive intervention will not only reduce the risk of developing MDD but also improve depression symptom severity at all levels of depression, as shown by a recent meta-analysis (pooled effect size g = 0.35, 95%-CI: 0.23–0.47; [23]). Fourth, uptake rates of a depression prevention intervention may be higher in a target population of patients with depressive symptoms, as treatment utilization was found to be associated with severity of baseline depression [24].

The internet is an appropriate prevention medium for scaling up preventive interventions as units of delivery are reasonably priced and can be easily administered [7, 25]. It has several additional advantages as discussed elsewhere [26–28].

In prior studies, Internet- and mobile-based interventions (IMI) have shown to be effective in the treatment of MDD [29, 30] as well as in the treatment of subthreshold depression, indicating their potential to be utilized for preventive interventions [25, 31–34]. Human support (guidance) has repeatedly been shown to have a positive effect on effectiveness of and adherence to IMIs [35, 36].

The proposed study aims to investigate the effectiveness and cost-effectiveness of an IMI (eSano BackCare-DP) to prevent the onset of depression for chronic back pain patients (PROD-BP) with subthreshold depressive symptoms. The study will be embedded into routine orthopedic care in order to examine the intervention’s effectiveness in an unselected sample of all eligible chronic back pain patients (i.e. the implementation will not be limited to a self-selected population of people who are already attracted to depression prevention interventions and the Internet). It is expected thateSano BackCare-DP is effective in preventing the onset of MDD compared to treatment as usual (TAU) over a 12-month follow-up period,eSano BackCare-DP is cost-effective compared to TAU.Compared to TAU, eSano BackCare-DP is superior in terms of (a) depression response, (b) work capacity, (c) quality of life, (d) pain related disability and (e) pain intensity.

Furthermore, the distributions of principal confounders in each group will be explored.

## Methods

### Study design

This project is a multicenter randomized controlled clinical trial (RCT) of parallel design comparing the effectiveness and cost-effectiveness of a guided depression prevention IMI with treatment as usual (TAU) (Fig. 1). All participants will receive TAU. Participants of the intervention group will additionally receive the IMI eSano BackCare-DP.

### Setting/Recruitment

Recruitment has started in October 2015. Recruitment will continue until the target sample size has been reached. Participants are recruited in the aftermaths of their orthopedic rehabilitation care. In order to increase the representativeness of our sample, we established two comparable recruitment strategies. First, back pain patients from eight orthopedic rehabilitation units are screened at admission and discharge. Clinical staff informs and recommends participation to patients screened positive (personal recruitment). In addition, an information flyer and a patient information form with a detailed description of the study process and information on the intervention are provided. Patients providing their informed consent are contacted by the study team in order to clarify further eligibility criteria by means of an online- and telephone assessment including a telephone administered clinical interview (SCID; [41–43]).

Second, back pain patients from orthopedic rehabilitation units across Germany receive a letter with the same information flyer and study process information (recruitment by letter). Interested back pain patients fill out an online PHQ-9 screening. Positive screened patients (PHQ-9 ≥ 5) providing their informed consent conduct the aforementioned online- and telephone assessment including a second PHQ-9 screening to ascertain persistent depression in line with the first recruitment strategy (second PHQ-9 ≥ 5). A third PHQ-9 screening takes place 2 months afterwards in case of only one PHQ-9 being screening positive. Eligible back pain patients from both recruitment strategies receive an email providing further information and a link referring to the intervention website. All participants are free to seek any additional help during the trial. Trial participants receive 15€ for the completed follow-up telephone assessment.

### Randomization

Participants eligible for inclusion will be randomly allocated to one of two groups (intervention or TAU). Randomization and allocation will be prepared in advance by a researcher ([name]) who is responsible for administration of the trial and participants. This researcher will remain blinded to all processes within the intervention. An automated, web-based randomization program (www.sealedenvelope.com) will be used, which features permuted block randomization, variable block sizes of 4,6,8 (randomly arranged), and an allocation ration of 1:1.

## Intervention

### Intervention condition

The intervention (eSano BackCare-DP) consists of six weekly sessions plus three optional modules and two booster sessions of approximately 45 to 60 min each (see Figs. 2 & 3). Participants can decide when to complete the booster sessions at the end of the last session. They can choose two dates within a timeframe of 3 months following the intervention, and will be reminded to log-in again. Sessions can be repeated as often as desired. All modules consist of information about depression and (chronic) back pain, provided by text, audio, and video, as well as assignments, metaphors and exercises. The content of the intervention is based on cognitive behavioral therapy (CBT) for depression, including elements of psychoeducation, social skills, problem solving, behavioral activation, improving self-care, relaxation and motivation for physical exercises. The intervention is based on prior interventions that have been evaluated in a number of RCTs in different samples [31, 34, 44–46]. We adapted and substantially extended the predecessors to the context of depression prevention and chronic back pain. In order to address chronic back pain patients specifically, psychological pain intervention elements are integrated in every module of the intervention. Moreover, three optional modules are offered, focusing on problems with sleep, partnership/sexuality and returning to the workplace. Emphasis is laid on homework assignments, which are intended to provide practice of learned skills. To enhance patient adherence, interactive elements (quizzes, conditional contents) are implemented. Participants will be asked about adverse events at the beginning of every session with the advice to check whether it is the right time to go on with the session. The intervention platform is provided by Minddistrict (www.minddistrict.com), a company specialized in the provision of web-based health interventions. Access to the platform proceeds through a unique username-password combination and will be available on a 24/7 basis. All transferred data will be secured based on ISO27001 and guidelines NEN7510.

**Fig. 2 Fig2:**
[figure not shown]
Intervention structure, technical implementations and support

**Fig. 3 Fig3:**
[figure not shown]
Intervention content, based on Cognitive Behavioral Therapy (CBT), including back pain specific self-management

### Text message coach

At the beginning of the training, participants are asked if they want to receive daily reinforcing text messages during the 6-week training period. Text message prompts have been shown to be beneficial in internet interventions with positive effects on efficacy and adherence [47–49]. The messages are sent automatically and coordinated with intervention content in order to integrate the learned techniques into daily life of the participants. Message content aims at reminding patients to complete homework assignments, repeating training content, and reinforcing motivation of participants.

### Control condition

Participants of the control condition will have unrestricted access to TAU. Although national treatment guidelines for low back pain and depression exist [50], TAU following orthopedic rehabilitation care may vary. There is no minimum treatment defined and TAU will not follow a standardized protocol; however, all received types of medical/psychological help during the last 3 months will be monitored with the Trimbos/iMTA questionnaire, to account for all costs associated with psychiatric illness (TIC-P) [51]. Using these data, an accurate description of TAU can be provided.

### Sample size/power calculation

The aim of the study is to compare the effectiveness of the intervention against TAU using a cox regression survival analysis with a significance level of 5%. Based on previous studies of depression incidence in chronic back pain patients and subclinical depression, we expect a mean incidence of MDD of 20% in the control group within the 12-months follow-up period [52–55]. Based on a prior conducted trial, we assume an absolute risk reduction of 9% with a respective hazard ratio of 0.522 between treatment and control group at 12 months after randomization [34]. A total of 64 events (event = onset of depression) need to be observed to detect a 47.8% decrease in hazard (hratio = 0.522) of the treatment group relative to the hazard of the control group based on a power of 80%. Accordingly, 406 participants (203 per group) need to be randomized (calculated using Stata/SE 13.1). The inclusion of relevant baseline predictors of depression onset will further increase power (e.g. baseline depression severity). Recruitment will be continued to allow for an expected attrition rate of 20%.

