## Statistical analysis

### Clinical analyses

All analyzes will be performed according to the intention-to-treat (ITT) principle. Kaplan-Meier curves and Cox proportional hazard regression analysis will be used to determine differences in time to onset of MDD in weeks between both study conditions over a follow-up period of 12 months. The dependent variable will be time to onset of MDD and treatment condition will be the independent variable. The proportional-hazards assumption will be tested based on the scaled Schoenfeld residuals test. Survival analysis assumes that censoring (i.e., a participant is lost-to-follow-up or completes the follow-up period without experiencing a major depressive episode) is non-informative. Non-informative implies that the reasons why participants drop out of the trial are unrelated to the study condition (i.e., participants in one study arm should not be routinely censored). We will apply the following methods to deal with informative censoring, if necessary: (a) imputation techniques for missing data, (b) sensitivity analyses to illustrate best and worst case scenarios to test the robustness of the base case findings and (c) the use of the drop-out event as a study end point [87]. In addition, the number needed-to-treat (NNT) to prevent one additional event in the intervention group versus the control group will be calculated [88]. Covariates will first be checked whether they are associated with the primary outcome, if not left out of the final analysis.

Secondary outcomes will be analyzed using hierarchical linear modeling. To examine potentially moderating covariates, correlation of covariates and outcome parameter are analyzed using multiple regression models. In addition, per protocol analysis will be performed to investigate the influence of drop-outs on study results. Missing data will be imputed using multiple imputation. Potential confounding factors between source population and study population will be assessed, which enables us to evaluate the external validity of the sample. Finally, characteristics of dropped out participants at follow-up will be inspected and resulting socio-demographic differences between intervention and control group will be described. A significance level of *p* ≤ .05 will be set for all analyses.

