The specific strengths of this study are the following: a) Prevention studies are regularly methodologically limited because they lack a diagnosis at baseline and/or follow-up [6]. By carrying out the SCID prior to study start and at 12-months follow-up a high content validity can be ensured. b) With a target sample of 406 participants, the study will be optimally powered, overcoming the small scale trial limitations of most prior prevention studies [6, 20]. Following the ITT principle contributes to reducing overestimation of clinical effectiveness. c) The intervention is specifically tailored to the special needs of the target group of chronic back pain patients. This has been discussed as having an uptake and adherence facilitating effect [27]. We aim to further facilitate adherence through the integration of the intervention into patients’ routine healthcare, which enables clinicians to inform participants about the characteristics and effectiveness of IMIs. This may have a positive impact on their acceptance [101]. d) Using the internet as the medium for prevention might allow for scaling up of preventive interventions on a public mental health level. e) The direct implementation of the intervention into the health-care system increases external validity in contrast to prior RCTs [31, 102].

High prevalence rates underscore that the integration of depression prevention into curative care systems for the medically ill is one of the major emerging global health challenges. If this study - the first of its kind – shows to be effective, the intervention could be implemented into general (chronic) back pain and mental health treatment protocols as well as adapted to other chronically ill patient groups, thus helping to reduce the disease burden of depression for both affected persons and society. Thus, the results of this study will be of major public health relevance.

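### The 64 events and 406 participants match a one-sided 5% calculation that is nowhere declared; at the usual two-sided 5% the stated 80% power is about 70–74%

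*Protocol article*

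**What the plan says.** All references are to the protocol article.

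- **Sample size/power calculation, test and level:** the comparison is made "using a cox regression survival analysis with a significance level of 5" per cent. Sidedness is not given.
- **Same section, control incidence:** "we expect a mean incidence of MDD of 20% in the control group within the 12-months follow-up period".
- **Same section, effect:** "we assume an absolute risk reduction of 9% with a respective hazard ratio of 0.522 between treatment and control group".
- **Same section, result:** "A total of 64 events (event = onset of depression) need to be observed to detect a 47.8% decrease in hazard (hratio = 0.522"). The power given for this event count is 80%. It is converted to 406 randomised participants, 203 per group, calculated in Stata. Baseline predictors are expected to add power, and recruitment is to continue to cover 20% attrition.
- **Clinical analyses:** the primary analysis is a Cox proportional hazards regression, and a level of p ≤ .05 "will be set for all analyses". No one-sided test is named.
- **Background:** the main hypothesis is that the intervention "is effective in preventing the onset of MDD compared to treatment as usual (TAU) over a 12-month follow-up period". The wording is directional, but no one-sided test is attached to it.
- **Discussion:** listed as a strength, "With a target sample of 406 participants, the study will be optimally powered".

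**The concern.** Sixty-four events are too few for 80% power at this hazard ratio if the 5% level is two-sided. A plain 5% level for a Cox coefficient is normally taken as two-sided, and the p-value in standard Cox output is two-sided. The event count therefore appears to come from a different test from the one a reader will assume.

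Two things are at stake. If the analysis is two-sided, a null result would be read as coming from a trial with a 20% chance of missing the planned effect, when that chance is 26–30%. If a one-sided 5% test is intended, the primary test is more lenient than readers will assume. Unless it is declared beforehand, its sidedness could be settled after the result is known.

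**Working it through.** **Inputs** (Sample size/power calculation; allocation ratio from Randomization): control incidence 0.20; absolute reduction 0.09, so 0.11 in the intervention arm; HR 0.522; power 80% (z = 0.8416); level 5% (z = 1.6449 one-sided, 1.9600 two-sided); 1:1 allocation.

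**Step 1. Hazard ratio and event probability.**
- HR = ln(0.89)/ln(0.80) = 0.5222, which agrees with the stated 0.522.
- Mean event probability = 1 − (0.80 + 0.80^0.522)/2 = 0.155.

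**Step 2. Reproducing the stated figures.** Freedman: E = (z_α + z_β)² × [(1 + HR)/(1 − HR)]², with [(1.522)/(0.478)]² = 10.14.
- One-sided 5%: (1.6449 + 0.8416)² = 6.183, so E = 6.183 × 10.14 = 62.68. That is 31.34 per arm, rounded up to 32 + 32 = **64 events**.
- N = 62.68/0.155 = 404.5. That is 202.2 per arm, rounded up to 203 + 203 = **406**.

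Both stated figures are matched.

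**Step 3. The same inputs under other formulas and at two-sided 5%.** Two-sided, (1.9600 + 0.8416)² = 7.849. Schoenfeld: E = 4(z_α + z_β)²/(ln HR)², with (ln 0.522)² = 0.4226.

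| Method | One-sided 5% | Two-sided 5% |
|---|---|---|
| Freedman | 62.68 events, N = 406 | 79.58, so 80 events, N ≈ 514 |
| Schoenfeld | 58.5, so 59 events, N ≈ 378 | 74.3, so 75 events, N ≈ 480 |
| Two proportions (20% v 11%) | 199 per arm (221 with continuity correction) | 253 per arm (275 with continuity correction) |
| Exponential survival | N ≈ 403–412 | N ≈ 511–523 |

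No two-sided entry is near 64 events or 406 participants.

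**Step 4. Two-sided power of the design as stated.**
- Freedman, 64 events: Φ(√64 × 0.478/1.522 − 1.960) = Φ(0.553) = 71.0%.
- Schoenfeld, 64 events: Φ(√64 × 0.6501/2 − 1.960) = Φ(0.640) = 73.9%.
- Expected events from 406 participants: 406 × 0.155 = 62.9, giving 70.2% (Freedman) and 73.2% (Schoenfeld).
- Two-proportion test, 203 per arm: 70.9%.
- For comparison, 64 events at one-sided 5% give 80.7% (Freedman) and 83.0% (Schoenfeld).

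**Step 5. Effect for which 64 events give 80% two-sided power.**
- Schoenfeld: HR = exp(−2 × 2.8016/8) = 0.496.
- Freedman: (1 + HR)/(1 − HR) = 8/2.8016 = 2.856, so HR = 0.481.

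The true hazard ratio would have to be about 0.48–0.50 or lower, against the planned 0.522.

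**The case against.** The strongest reply is that the article never says two-sided. Its hypotheses are directional, and the exact match suggests that a one-sided 5% calculation was deliberate; in that case 80% is right. The article is also a condensed account, and sidedness may be set out in a fuller protocol or analysis plan. Part of this stands: the 70–74% figure depends on reading the 5% level as two-sided, and silence on sidedness alone would not be a finding. But the printed event count and sample size do not deliver the printed power under the ordinary reading of the printed level. Superiority hypotheses are usually worded directionally without implying a one-sided test. Whichever reading was meant, the text needs correcting.

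Two further replies do not rescue the figure:

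- **Baseline predictors.** Their gain is unquantified and offered on top of the 80%. The Clinical analyses section also drops covariates not associated with the outcome. The 70–74% is accordingly an unadjusted figure.
- **Recruitment to cover attrition.** Allowing for 20% loss means about 406/0.80 = 508 randomised, which restores about 406 analysable participants, not 480–514. If 406 already included attrition, about 406 × 0.80 × 0.155 = 50 events would be expected, and two-sided power would be about 61–64%.

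It can also be said that the Discussion's phrase only contrasts this trial with smaller ones. That edit is secondary to the correction of the power statement.

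**Conclusion.** The concern holds. The one-sided origin is inferred from the arithmetic, not stated in the article, but the inference is firm: one standard calculation returns both printed figures exactly, and every two-sided variant tried needs at least 75 events and about 480 participants. With the 5% level read as two-sided, an unadjusted analysis, HR 0.522 and 20% control incidence, power is about 71–74% at 64 events and 70–73% at the 62.9 events expected from 406 participants. The shortfall is roughly 6–10 percentage points. If a one-sided 5% test was intended, the 80% is correct and the fault is that the test is not declared. Since this is the power claim for the primary endpoint, it must be corrected.

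**What to change.** State the sidedness of the primary test in Sample size/power calculation and in Clinical analyses, then follow the branch that applies:

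- **Two-sided 5%:** replace the power statement with one saying that 64 events give about 71–74% power for HR 0.522, and that 80% power would need 75–80 events.
- **One-sided 5%:** say so explicitly in both sections and report the primary result as such.

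The Discussion's statement about power at 406 participants should be removed or brought into line.

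The cost is wording only, and on the two-sided branch a less favourable power figure. No extra participants are needed to correct the statement. Actually reaching 80% two-sided power would be a separate decision: about 480–514 analysable participants, or about 600–643 randomised after dividing by 0.80 for attrition.

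### The sample size of 406 has no allowance for loss; the plan promises further recruitment for 20% attrition but gives 406 as its only target

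*Protocol article*

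**What the plan says.** The section Sample size/power calculation plans a comparison "using a cox regression survival analysis with a significance level of 5" per cent and a requirement of 64 events "based on a power of 80" per cent. On the control arm it says "we expect a mean incidence of MDD of 20% in the control group within the 12-months follow-up period", and it assumes an absolute reduction of 9 percentage points, with a hazard ratio of 0.522. It then states: "Accordingly, 406 participants (203 per group) need to be randomized". The section closes with: "Recruitment will be continued to allow for an expected attrition rate of 20" per cent. No number follows.

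Three other places bear on the target:

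- Abstract, Methods: "A total of 406 patients with chronic back pain and without a depressive disorder at baseline will be recruited", and these patients are then allocated to the two arms.
- Setting/Recruitment: "Recruitment will continue until the target sample size has been reached". No figure is attached.
- Discussion, strengths of the study: "With a target sample of 406 participants", at which size the trial is said to have optimal power.

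The Assessments section and Table 1 place the diagnostic interview (SCID) at baseline and 12 months only. The section on the primary outcome dates onset by a life chart recalled over the follow-up period.

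**The concern.** A recruitment target governs when a trial stops enrolling, and the power claim depends on it. Here the two are not tied to the same number. If 406 is what the calculation needs with complete outcome data, and 20% attrition is expected, the number to randomise must be larger. The sample size section says that recruitment will go on for this reason, but the abstract and the Discussion present 406 as the final total. The rule in Setting/Recruitment refers to a target without a figure, and the only figure a reader can find is 406.

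A reader, a monitor or the data monitoring board therefore cannot tell from the article whether enrolment ends at 406 or at about 500. In the first case the event requirement and the stated power are not met. In the second, the abstract and the Discussion give the wrong total.

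**Working it through.** **Inputs, all from Sample size/power calculation:** control incidence 0.20; absolute reduction 0.09, hence 0.11 in the intervention arm; hazard ratio 0.522; power 80%; significance level 5%, sidedness not stated; 64 events; 406 randomised; attrition 20%. Allocation is 1:1 (Randomization).

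**1. Reproducing the plan's figures.**

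- Hazard ratio: ln(1 − 0.11) / ln(1 − 0.20) = 0.522. This agrees with the plan.
- Mean event rate: (0.20 + 0.11) / 2 = 0.155.
- Events by the Freedman formula, one-sided 5%: (1.645 + 0.842)² × [(1 + 0.522) / (1 − 0.522)]² = 62.7, rounded up to 63.
- Participants: 62.7 / 0.155 = 404; 63 / 0.155 = 406.

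This matches 406, and it matches 64 events to within rounding. The one-sided Schoenfeld formula (59 events, about 378 participants) does not match.

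**2. Does 406 contain an allowance for loss?**

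406 × 0.155 = 62.9 events. The requirement is met, within rounding, only if all 406 supply an outcome. This check needs neither a formula for events nor a choice of sidedness. If 406 already included 20% loss, the remaining 325 participants would need an event rate of 64 / 324.8 = 0.197, well above the planned mean of 0.155.

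**3. If recruitment stops at 406 and 20% are lost.**

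- Participants with an outcome: 406 × 0.80 = 324.8, about 325.
- Events: 324.8 × 0.155 = 50.3, against 64 required (50.3 / 64 = 0.79).

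This takes a lost participant to contribute no event. That fits the design, because someone who misses the 12-month interview has neither a diagnosis nor a dated onset. As a more generous assumption, let lost participants be observed for half the follow-up: 406 × (0.80 + 0.10) × 0.155 = 56.6 events, still below 64.

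**4. Power on the basis that reproduced the plan (Freedman, one-sided 5%).**

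Power = Φ[√events × (1 − 0.522) / (1 + 0.522) − 1.645].

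| Case | Events | Power |
|---|---|---|
| 406, no loss | 62.9 | 80% |
| 406, lost participants observed for half the follow-up (assumption) | 56.6 | 76% |
| 406, 20% lost with no event information | 50.3 | 72% |

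**5. The number the attrition sentence implies.**

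- From 406 with outcome data: 406 / 0.80 = 507.5, so 508 randomised, giving 508 × 0.80 × 0.155 = 63.0 events.
- From a full 64 events: 64 / 0.155 = 412.9, so 413; 413 / 0.80 = 516.25, so 517 randomised.

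Neither 508 nor 517, nor any other number above 406, appears in the article.

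**The case against.** The strongest reply is that the sample size section does deal with attrition: having derived 406, it says recruitment will continue to cover 20% loss. The natural reading is enrolment beyond 406, and the rule in Setting/Recruitment, which carries no figure, can be read the same way. The shortfall then never arises. Much of this stands. A reader might infer that the trial overlooked attrition, or that it will miss its event requirement by a fifth. The text supports neither inference, because the loss of events is conditional on stopping at 406. What the reply does not remove is that two other sections give 406 as the total recruited and as the target, and that the intended larger number is never stated.

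A second reply is that a condensed article may leave the inflated figure to the full protocol. Absence alone would indeed be no finding. The point here is a conflict between statements that the article does make.

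Third, the section on intervention satisfaction and adherence defines attrition rate by log-in data, and people who stop using the programme can still give a 12-month interview. But non-use of the programme is no reason to recruit more participants for an intention-to-treat comparison, so loss of outcome data is the reading that fits a sample size allowance.

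Fourth, the statistical analysis section plans imputation and best-case and worst-case analyses. These help to handle missing outcomes, but they do not restore observed events.

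**Conclusion.** The concern holds as an inconsistency in the stated target, of moderate severity. The figure of 406 has no attrition allowance, the plan expects 20% attrition, and 406 is nevertheless the only target given. If enrolment ended there, about 50 events would be expected in place of 64 (about 57 on the half-follow-up assumption). Power would be about 72% against the planned 80%. These figures rest on the plan's own incidence, effect and attrition assumptions, on attrition meaning a missed 12-month interview, and on the one-sided Freedman basis, which is inferred by back-calculation. If the team in fact enrols about 508, the shortfall disappears and only the inconsistent reporting remains.

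Two stronger readings should be set aside. This is not an arithmetic error: the hazard ratio, the events and 406 agree with one another within rounding. Nor does the article say that the test is one-sided. The sidedness of the 5% level is a separate question, and power losses that come from it should not be added to this point.

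**What to change.** State one randomisation target and use it in the abstract, Setting/Recruitment, Sample size/power calculation and the Discussion. There are two consistent ways to do so:

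1. Give the inflated number that the attrition sentence implies, 508 (or 517 if a full 64 events is wanted after loss). Describe 406 (or 413) as the number needed with outcome data, and put the figure into the recruitment rule.
2. If 406 is the true randomisation target, delete the attrition sentence with its promise of continued recruitment. Restate the expected events after 20% loss (about 50) and the reduced power, and amend the Discussion's claim of optimal power.

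Either is a change of wording. The first adds no recruitment beyond what the sample size section already announces: 508 − 406 = 102 participants. The second adds none, but gives up the stated 80% power.
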